## Abstract

**Introduction:**

Following the detection of fetal growth restriction, there is no consensus about the criteria that should trigger delivery in the late preterm period. The consequences of inappropriate early or late delivery are potentially important yet practice varies widely around the world, with abnormal findings from fetal heart rate monitoring invariably leading to delivery. Indices derived from fetal cerebral Doppler examination may guide such decisions although there are few studies in this area. We propose a randomised, controlled trial to establish the optimum method of timing delivery between 32 weeks and 36 weeks 6 days of gestation. We hypothesise that delivery on evidence of cerebral blood flow redistribution reduces a composite of perinatal poor outcome, death and short-term hypoxia-related morbidity, with no worsening of neurodevelopmental outcome at 2 years.

**Methods and analysis:**

Women with non-anomalous singleton pregnancies 32+0 to 36+6 weeks of gestation in whom the estimated fetal weight or abdominal circumference is <10th percentile or has decreased by 50 percentiles since 18–32 weeks will be included for observational data collection. Participants will be randomised if cerebral blood flow redistribution is identified, based on umbilical to middle cerebral artery pulsatility index ratio values. Computerised cardiotocography (cCTG) must show normal fetal heart rate short term variation (≥4.5 msec) and absence of decelerations at randomisation. Randomisation will be 1:1 to immediate delivery or delayed delivery (based on cCTG abnormalities or other worsening fetal condition). The primary outcome is poor condition at birth and/or fetal or neonatal death and/or major neonatal morbidity, the secondary non-inferiority outcome is 2-year infant general health and neurodevelopmental outcome based on the Parent Report of Children’s Abilities-Revised questionnaire.

**Ethics and dissemination:**

The Study Coordination Centre has obtained approval from London-Riverside Research Ethics Committee (REC) and Health Regulatory Authority (HRA). Publication will be in line with NIHR Open Access policy.

**Trial registration number:**

Main sponsor: Imperial College London, Reference: 19QC5491. Funders: NIHR HTA, Reference: 127 976. Study coordination centre: Imperial College Healthcare NHS Trust, [name] with Centre for Trials Research, College of Biomedical & Life Sciences, Cardiff University. IRAS Project ID: 266 400. REC reference: 20/LO/0031. ISRCTN registry: 76 016 200.

Strengths and limitations of this studyChanges in cerebral Doppler measures are considered a strong candidate for triggering delivery following detection of late preterm fetal growth restriction.The primary outcome is a composite of perinatal and neonatal outcome, and infants will be followed to determine health and neurodevelopment at 2 years to ensure safety and non-inferiority of intervention.This appropriately powered UK and European multicentre trial will inform NHS policy and the findings will be generalisable to late preterm fetal growth restriction in other healthcare systems.There are limited data available in respect of selecting the threshold of cerebral Doppler change for randomisation.Some non-UK centres will not randomise women at the earlier gestation range (32–33+6 weeks) and this could limit the generalisability of the results in this group of women.

## Introduction

Third trimester poor fetal growth and compromise are strongly associated with stillbirth, neonatal illness^1^ and an increased risk of fetal or neonatal brain injury.^2^ The only therapeutic option is delivery of the fetus. This poses a dilemma: delivery too early may incur the complications of prematurity, delivery too late risks further fetal compromise, brain injury and late stillbirth. The problem of when to deliver these babies is twofold: there is no consensus on how to identify fetal compromise and there is no ‘ideal’ evidence-based monitoring strategy. Current screening strategies include standardised symphysis-fundal height measurement, third trimester ultrasound and umbilical Doppler velocimetry.^3 4^ National Institute for Health and Care Excellence (NICE) acknowledges that methods to identify fetal growth restriction (FGR) are ‘poorly developed or not tested by rigorous methodology’.

The use of Doppler ultrasound of fetal vessels allows non-invasive assessment of blood flow. Fetal ‘cerebral blood flow redistribution’, prioritising blood flow toward the brain at the expense of other organs, is a response to an adverse intrauterine environment characterised by hypoxaemia. Ultrasound markers of such fetal compromise include Doppler assessment of blood flow velocity^5–7^ and abdominal circumference growth velocity ‘drop off’ in the third trimester.^8 9^ Intervention by delivery of the fetus in response to either evidence of blood flow redistribution or fetal growth slowing has never been tested in a randomised trial. Computerised cardiotocography (cCTG) has been used in several observational studies to determine fetal condition in relation to hypoxaemia and acidosis. The RCOG (Royal College of Obstetricians and Gynaecologists) recommends that research is required to evaluate the effectiveness of third trimester ultrasound assessment, concluding that ‘middle cerebral artery (MCA) Doppler may be a more useful test in small for gestational age (SGA) fetuses detected after 32 weeks’^4^ but does not define parameters that should trigger delivery. Even with effective screening for FGR, the questions of how to monitor and when to deliver would remain.

A Cochrane review of the management of ‘compromised babies’ at term showed no difference in perinatal or long-term outcome with a policy of early delivery versus conservative management.^10^ Only three trials were included: two included small babies, both part of the DIGITAT (Disproportionate Intrauterine Growth Intervention Trial At Term) study (a small pilot and the main trial),^11^ the third included babies with reduced amniotic fluid. There is no Cochrane review on the optimal timing of delivery in late preterm growth restricted babies.

A systematic review included only one trial of timed delivery in late preterm babies. The Growth Restriction Intervention Trial^12^ included 547 babies from 24 to 36 weeks of gestation with evidence of preterm growth restriction or compromise, where there was clinical uncertainty whether immediate delivery was indicated. Of these, 210 babies were recruited between 33+0 and 36+6 weeks: 107 women were randomised to early delivery and 103 to delayed delivery. Mortality and a range of neurodevelopmental measures were similar between the groups. These results cannot be used to inform management because of the small number of infants assessed using only umbilical artery Doppler velocimetry, the subjective assessment of the cardiotocograph (ie, not computerised analysis), and the use of clinician’s discretion rather than standardised management.

Results from our previous randomised trial of delivery decision-making using Doppler velocimetry and cCTG in pregnancies with FGR at 26–32 weeks of gestation—the TRial of Umbilical Fetal FLow in Europe (TRUFFLE) provided evidence associating monitoring strategies with improved outcomes^13^ and guides practice internationally.^14 15^ In TRUFFLE (2005–2010) we studied FGR <32 weeks of gestation using cCTG as the standard of care for timing delivery, compared with early or late fetal ductus venosus (DV) Doppler velocimetry changes with a cCTG ‘safety net’. Surviving infants whose mothers had been randomised to delivery in late DV changes arm showed better neurodevelopment at 2 years of age.^13^

We then carried out the prospective multicentre observational TRUFFLE 2 Feasibility Study (2017–2018, n=1024). A range of markers of cerebral redistribution were evaluated as potential delivery trigger points in two gestational age bands. These included the MCA Doppler and the umbilical cerebral ratio (UCR); calculated by dividing the Doppler pulsatility index of the umbilical artery by that of the MCA. Participating clinicians suggested greater concern about fetal condition is required to trigger delivery at earlier rather than later gestational ages between 32 and 36 weeks. We, therefore, selected a more abnormal threshold for cerebral redistribution at earlier gestational ages, based on stepped UCR z-score values.^16^ Of note was the finding from a prospective study that birth condition, fetal mortality and neonatal morbidity rate were more common among fetuses showing higher UCR z-score, indicating cerebral redistribution, compared with those with a lower UCR z-score (15 vs 9%).^17^

On this basis, we designed this randomised trial of delivery for women identified with late preterm FGR, to test the hypothesis that delivery based on UCR values derived from the feasibility study will safely lead to improved fetal outcomes (TRUFFLE 2).

## Methods and analysis

### Study design

This is an individual unblinded randomised trial of pregnant women experiencing FGR. Following informed consent, 1560 women will be randomised to either immediate or delayed delivery. Women are being recruited from UK and European centres.

Potential participants are women with singleton non-anomalous pregnancies between 32+0 and 36+6 weeks of gestation in whom a SGA fetus is identified or one whose growth has slowed. This is defined as estimated fetal weight or abdominal circumference <10th percentile and/or having decreased by 50 percentiles since an ultrasound scan at 18–32 weeks. Biometry must have been performed in the 14 days prior to inclusion. Each centre will use local growth charts. Data is collected on absolute measurements and growth chart-derived percentiles. Once identified as potential participants women receive regular monitoring as per local standard of care for fetal condition, using ultrasound biometry, umbilical and MCA Doppler velocimetry assessments and cCTG (using Dawes-Redman criteria). This is recommended to be repeated every 14 days; these observational data are recorded.

Women become eligible for randomisation when signs of fetal cerebral blood flow redistribution are detected by Doppler, defined below and shown in the study flow chart (online supplemental file 1—flow chart).

10.1136/bmjopen-2021-055543.supp1Supplementary data

Delivery is based on UCR pulsatility index z-scores, of >1.5 (between 32+0 and 33+6 weeks) or >1.0 (34+0 to 36+6 weeks). These correspond to an absolute UCR of ≥1.0 at 32+0 to 33+6 weeks and ≥0.8 at 34+0 to 36+6 weeks. Abnormal UCR measurements must be repeated within 15 minutes–24 hours to confirm these values. This need not be consecutive, so that if the second measurement is normal the patient may still be randomised if a repeat Doppler measurement is abnormal within 72 hours of the first abnormal measurement. Randomisation will occur at the time of the second qualifying UCR measurement and is stratified by centre and gestational age. Randomisation is through the CASTOR website (Amsterdam, NL) into which eligibility, monitoring and outcome data are entered.

Women are consented in a two-stage process. Stage 1 (pre-eligible) consent is not a prerequisite and women may be consented directly for randomisation with stage 2 (eligible for randomisation) consent.

#### Pre-eligible: consent for observational data collection

Consented for prospective data collection once identified as meeting criteria for SGA or slowed fetal growth (as defined above) but not meeting cerebral Doppler thresholds for randomisation or not willing to be randomised. This will include demographics, medical history, ultrasound findings and outcomes. This consent will include obtaining a personal email address, which is entered into and stored on Castor, and willingness to be contacted in the future for follow-up where women are randomised (online supplemental file 2—consent form for observational data collection).

10.1136/bmjopen-2021-055543.supp2Supplementary data

#### Eligible for randomisation: consent for randomisation

Consent for randomisation once cerebral redistribution is identified, with UCR (as defined above) of ≥1.0 at 32+0 to 33+6 weeks and ≥0.8 at 34+0 to 36+6 weeks. This consent will also include contact details and willingness to be contacted in the future for follow-up data collection (online supplemental file 3—consent for randomisation).

10.1136/bmjopen-2021-055543.supp3Supplementary data

Women are randomly allocated to either immediate delivery or delayed delivery as defined below. Randomisation has a 1:1 allocation ratio and stratified based on gestational age (above or below 34 weeks) and centre. Randomisation is conducted on the electronic data capture platform (Castor EDC, Amsterdam, The Netherlands).

#### Immediate delivery

Participants in the immediate delivery arm will be delivered by Caesarean or induction of labour will be commenced within 48 hours, allowing for administration of corticosteroids and infusion of magnesium sulphate as per local protocol and guidance. Start of induction of labour is defined as administering cervical preparation (cervical balloon, prostaglandins, etc), artificial rupture of membranes or administration of oxytocin.

#### Delayed delivery

Participants in the delayed delivery arm will be monitored using twice weekly Doppler and cCTG monitoring, or more frequently based on local clinical protocols if required. Umbilical artery Doppler velocities may be measured in this time and delivery may be based on these safety net criteria (see box below). We strongly recommend that MCA measurements are not undertaken during monitoring in the delayed delivery arm. Delivery is indicated when short term variation (STV) is <4.5 ms on cCTG or there are repeated fetal heart rate decelerations. Once participants reach 37+0 weeks of gestation the delivery plan will be based on local protocols.

Box 1Delivery thresholds based on umbilical artery Doppler for participants in all arms of the studyUmbilical Doppler delivery thresholds.In all arms absolute indications for delivery include:Umbilical artery Doppler with reversed end diastolic flow after entry into the trial, ORUmbilical artery Doppler absent end diastolic flow from 34+0 weeks.

### Study timeline

Study setup: 0–10 months; recruitment/randomisation: 11–36 months. Two years follow-up questionnaires 35–60 months; analyses, writing up, reporting and dissemination: 61–66 months. This equates to 5 and ½ years (66 months).

### Study outcome measures

#### Primary outcome

The primary outcome for the study is a composite of fetal or infant death, composite measure of poor condition at birth and neonatal morbidity—as defined by presence of any of the following:

Poor condition at birthApgar score at 5 min <7, umbilical artery pH <7.0 or umbilical vein pH <7.1.Need for resuscitation with intubation, chest compressions or medication.Fetal death/ death before neonatal hospital dischargeNeonatal brain injury syndromesInfants with a diagnosis consistent with hypoxic ischaemic encephalopathy (HIE): term and near-term infants only.Infants with a diagnosis of intracranial haemorrhage, perinatal stroke, HIE, central nervous system infection, or kernicterus (bilirubin encephalopathy): all infants.Preterm white matter disease (periventricular leukomalacia): preterm infants only.Infants with a recorded seizure confirmed by Electro-encephalogram (EEG).Respiratory supportNeed for mechanical support of respiration after admission to neonatal unit (NNU), for more than 1 hour; includes need for continuous positive airways pressure (or NIPPV; Noninvasive positive-pressure ventilation) or mechanical ventilation via endotracheal tube but excludes need for supplemental oxygen.Cardiovascular abnormalityHypotensive treatment, patent ductus arteriosus requiring treatment, or disseminated coagulopathy.SepsisClinical sepsis with positive blood culture.necrotising enterocolitis requiring surgery.Retinopathy of prematurity requiring treatment (laser or anti Vascular Endothelial Growth Factor (VEGF) injections)

#### Secondary outcomes

##### For the baby

Health and developmental outcomes—assessed using Parent Report of Children’s Abilities-Revised (PARCA-R) questionnaire at 2 years corrected age and an Infant Health Questionnaire up to 2 years (online supplemental file 4—PARCA-R Questionnaire and online supplemental file 5—Infant Health Questionaire).

10.1136/bmjopen-2021-055543.supp4Supplementary data

10.1136/bmjopen-2021-055543.supp5Supplementary data

The PARCA-R^18^ will be completed at 24 months term-equivalent age, this allows derivation of the non-verbal cognitive scale and language development scale. Raw scores from the scales are standardised (by corrected age and gender) to a notional population mean of 100 (SD=15) and the average of these two component scores will be taken as the overall composite score. Corrected age is used for preterm babies (born before 37 weeks) and represents the age of the child from the estimated date of delivery.

The Infant Health Questionnaire^19^ will be used to derive the following health outcomes at 6, 12, 18 and 24 months post partum:

Use of any hospital service (yes/no) and total number of contacts over the 2-year period.Admitted to hospital (yes/no) and total number of admissions over the 2-year period.Planned/unplanned admissions to hospital (yes/no) over the 2-year period.Intensive care or not over the 2-year period.Attended emergency department (and not subsequently admitted) (yes/no) over the 2-year period.Attended Outpatients/clinic (yes/no) over the 2-year period.

##### For the mother

Gestational hypertension developed post study entryAs defined by the International Society for Study of Hypertension in pregnancy (ISSHP):^20^ hypertension (blood pressure ≥140/90 mm Hg) arising de novo after 20 weeks gestation in the absence of proteinuria.Pre-eclampsia developed post study entryAs defined by the ISSHP:^20^ blood pressure ≥140/90 mm Hg and significant proteinuria (protein/creatinine ratio of 30 mg/mmol or more).Onset of labour (spontaneous, induction (method), prelabour caesarean section).Mode of delivery (spontaneous vaginal, assisted vaginal, caesarean section).

### Doppler quality control

#### Sonographer standardisation

Each sonographer in each centre taking part in the trial are assessed by the local principal investigator (PI). Each sonographer will submit to the local PI two images: pseudo anonymised ultrasound images for each Doppler parameter (umbilical artery and MCA) each showing a colour Doppler image with the gate placed over the vessel, and the pulsed wave Doppler waveform arising from that image. The local PI will determine whether these images are satisfactory using a predefined quality control scoring system (online supplemental file 6—Doppler image scoring sheet).

10.1136/bmjopen-2021-055543.supp6Supplementary data

#### Doppler ultrasound criteria

Measurements are obtained in fetuses between 32+0 and 36+6 weeks of gestation. Umbilical artery and MCA pulsatility index images are collected according to specific predefined objective criteria for both the colour Doppler images and pulsed wave Doppler.

#### Doppler quality control

The local PI will provide details of all sonographers having undergone standardisation in that centre to the Centre for Trials Research (CTR). The CTR will independently request all images submitted to the local PI for the first five patients randomised from each unit, and then for up to 10% of patients thereafter, for anonymised quality control assessment by the Quality Control Board. All images are collected as pseudo anonymised.jpeg images and saved electronically in a Doppler ultrasound sonographer standardisation file by the PI, with the submitting sonographer identifiable. Images are scored using the predefined scoring criteria. The CTR will manage this process and will provide feedback if necessary, and ensure that members of the TRUFFLE 2 Quality Control Board do not assess images from their own unit.

### Participant entry

#### Preregistration evaluations

Ultrasound scan of fetal growth between 30+0 and 36+6 weeks of gestation, including measurement of MCA and umbilical artery Doppler velocities.cCTG STV analysed using Dawes-Redman criteria.

#### Inclusion criteria

(All criteria should be fulfilled to be eligible for randomisation)

Women ≥18 years old.Pregnant with singleton non-anomalous fetus.Between 32+0 and 36+6 weeks of gestation.Estimated fetal weight or abdominal circumference <10 th percentile OR decreased by 50 percentiles since an ultrasound scan at 18+0–32+0 weeks.Cerebral redistribution defined as UCR ≥1.0 (between 32+0 and 33+6 weeks) or ≥0.8 (34+0 to 36+6 weeks) repeated within 15 minutes–24 hours.Normal STV on cCTG (4.5 msec or above).

#### Exclusion criteria

Indication for immediate delivery required within 48 hours.Unable to give informed consent.Preterm prelabour rupture of the membranes.Suspected placental abruption or antepartum haemorrhage.Presence of reversed end diastolic flow in the umbilical artery.

### Assessment and follow-up

Assessment of the primary outcome is at infant discharge from the NNU and assessment of the key secondary infant outcomes will use the Infant Health Questionnaire and PARCA-R. The Infant Health Questionnaire will be sent out by investigators via Castor at 6, 12, 18 and 24 months post partum. Neurodevelopment is assessed at 2 years age corrected for prematurity using the PARCA-R, also sent via Castor (translated into local language). The window for determining 2-year outcome is from 23.5 to 27.5 months over which range the PARCA-R has been standardised.

Endpoint is 30 months after the estimated date of delivery of the last participant to deliver (24 months follow-up with additional 6 months for data cleaning and additional enquiries).

### Statistics and data analysis

#### Sample size

The trial is powered to detect if immediate delivery following cerebral redistribution is superior to expectant management following cerebral redistribution on this outcome. A difference in the proportion with the primary outcome from 15% in the delayed delivery to 9% in the immediate delivery (from TRUFFLE 2 feasibility study) demonstrates an OR of 0.56. At two-sided 5% significance with 95% power, 780 participants per arm are required, giving 1560 in total. Given the immediacy of this outcome, no loss to follow-up is expected. An important non-inferiority secondary safety outcome is infant neurodevelopment, which is measured by parent completed questionnaire at 2 years using the PARCA-R, as recommended in NICE Guidance,^21^ supplemented by infant health information over the intervening 2 years. Assuming a loss to follow-up at 2 years of 20%, 2-year outcomes for approximately 1248 infants are expected (624 per group assuming no difference in the lost to follow-up between the groups). The PARCA-R questionnaire provides a composite score for neurodevelopment with a standardised mean of 100 and SD of 15. With a one-sided significance level of 1%, under a non-inferiority hypothesis, a sample size of 624 in each group achieves a 98% power to detect a non-inferiority margin of difference in the mean PARCA-R score of no less than four points (0.25 of a SD). A margin of no less than three points can be detected with 90% power.

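### The PARCA-R non-inferiority margin is given as four points and as 0.25 SD, which differ on the protocol's own SD of 15; the averaged composite need not have that SD, and the stated powers do not quite match.

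*Protocol article*

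**What the plan says.** The protocol article treats 2-year neurodevelopment as an important non-inferiority safety outcome. Under Sample size it describes the score: "The PARCA-R questionnaire provides a composite score for neurodevelopment with a standardised mean of 100 and SD of 15". The test level follows: "With a one-sided significance level of 1%, under a non-inferiority hypothesis". The power claim is that "a sample size of 624 in each group achieves a 98% power" for "a non-inferiority margin of difference in the mean PARCA-R score of no less than four points (0.25 of a SD", the gloss closing there. The next sentence adds: "A margin of no less than three points can be detected with 90% power". The 624 per arm comes from 20% attrition: "Assuming a loss to follow-up at 2 years of 20%, 2-year outcomes for approximately 1248 infants are expected".

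Under Secondary outcomes, For the baby, the score is built in two steps. First, "Raw scores from the scales are standardised (by corrected age and gender) to a notional population mean of 100 (SD=15"; then "the average of these two component scores will be taken as the overall composite score". No step is described that rescales the average to an SD of 15.

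Under Main analysis, non-inferiority is to be judged from a one-sided 95% confidence interval for the difference in mean PARCA-R. The margin is not repeated there.

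**The concern.** A non-inferiority margin is the decision threshold. Here one phrase describes it in two ways that do not agree on the SD given two sentences before, and the stated power fits the description in SD units better than the one in points. An SAP author could defend either value from this text.

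The SD itself is also in doubt. If the score analysed is a simple average of two scales, it is less variable than either scale unless they correlate perfectly. Four points is then a larger fraction of an SD than the protocol says, so the margin looks stricter in SD units than it is. The outcome is infant neurodevelopment after a policy of earlier delivery, so the threshold should be unambiguous before anyone sees the results.

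**Working it through.** **Inputs.** From Sample size: n = 624 per arm (1560 × 0.8 = 1248, halved), SD 15, one-sided 1% (z = 2.326), margins of 4 points, 0.25 SD and 3 points, stated powers 98% and 90%. From Main analysis: one-sided 95% limit (z = 1.645). From For the baby: two scales, each SD 15, averaged. Assumed: true difference 0. The correlation r between the scales is not given, so a range is used.

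**1. The two descriptions of the margin.** 0.25 × 15 = 3.75 points; 4/15 = 0.267 SD. They coincide only if the SD is 4/0.25 = 16, which the protocol does not state.

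**2. The stated powers.** SE = 15 × √(2/624) = 0.849. Power = Φ(margin/SE − 2.326).

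| Margin (points) | Margin/SE | Power | Stated |
|---|---|---|---|
| 4 | 4.710 | 99.1% | 98% |
| 3.75 | 4.416 | 98.2% | 98% |
| 3 | 3.533 | 88.6% | 90% |

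The noncentral t gives the same to within 0.1 percentage point. The 98% is therefore the figure for 0.25 SD. For three points, 90% would need 651 per arm: 2 × 15² × (2.326 + 1.282)²/3² ≈ 651.

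**3. SD of the averaged composite.** For two scales of SD 15 with correlation r, the SD of the average is 15 × √((1 + r)/2).

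| r (assumed) | SD of average | 0.25 SD (points) | 4 points in SD | Power at 3 points | Power at 4 points |
|---|---|---|---|---|---|
| 0.5 | 12.99 | 3.25 | 0.308 | 96.0% | 99.9% |
| 0.6 | 13.42 | 3.35 | 0.298 | 94.8% | 99.8% |
| 0.7 | 13.83 | 3.46 | 0.289 | 93.4% | 99.7% |
| 0.8 | 14.23 | 3.56 | 0.281 | 91.9% | 99.6% |
| 1.0 | 15.00 | 3.75 | 0.267 | 88.6% | 99.1% |

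The SD reaches 15 only at r = 1. A smaller SD raises power for any margin fixed in points. What changes is the meaning of 0.25 SD.

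**4. Effect on the conclusion.** Under the one-sided 95% limit with SD 15, the largest observed deficit that still passes is margin − 1.645 × 0.849 = margin − 1.40.

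- Margin 4: 2.60 points.
- Margin 3.75: 2.35 points.

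An observed deficit between about 2.35 and 2.60 points is non-inferior under one reading and not under the other. An observed deficit of 2.0 has its limit at −2.0 − 1.40 = −3.40 and passes under both.

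**The case against.** The best defence is that the protocol states one margin, in points, and that figure is four. On this view the SD gloss is a rounded aid to interpretation, since 0.267 is close to 0.25. The two readings differ by a quarter of a point and disagree only in a narrow band of results. The powers are right to within about 1.5 percentage points, and the 98% understates power at four points, which does no harm. The SD in growth-restricted infants may in any case differ from the norm value.

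Much of this stands. A reader might infer that the protocol leaves three rival margins open and so fixes no threshold. The text does not support that: four points is explicit, and the three-point sentence reads as an added power statement. A reader might also infer that the trial is underpowered for this outcome. It is not: at one-sided 1%, power at SD 15 is 98.2% or 99.1% for either reading of the margin, and a smaller composite SD only raises it. Nor is it a defect in itself that Main analysis does not repeat the margin, because the protocol defers analysis detail to the SAP.

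The defence does not remove the inconsistency. The 98% belongs to the reading in SD units, so the gloss cannot simply be dismissed as loose rounding of four. The SD attributed to the composite also does not follow from how the composite is built.

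**Conclusion.** The point holds as an inconsistency in the stated margin, its SD equivalent and the accompanying powers. It is not a failure of the design. On SD 15 the two descriptions differ by 0.25 points, and the choice changes the conclusion for observed deficits of about 2.35 to 2.60 points under the one-sided 95% rule. That band assumes SD 15, 624 per arm and a simple two-sample SE, without covariate or centre adjustment.

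The mismatch between an SD of 15 and a plain average follows from the definitions, unless the average is re-standardised. Its size does not: the 13.0 to 14.2 range, and four points as 0.28 to 0.31 SD, rest on an assumed correlation of 0.5 to 0.8. The documents do not settle whether 4 or 3.75 is intended. Choosing 3.75 on the strength of a rounded power figure would carry over the same doubtful SD.

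Separately, the power calculation uses one-sided 1% while the analysis uses a one-sided 95% interval; that difference is not part of this point.

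**What to change.** Before database lock:

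- State one margin in PARCA-R points under Sample size and use the same figure in the non-inferiority rule under Main analysis.
- Give its SD equivalent from the SD of the averaged composite, with the source of that SD, or state that the composite is re-standardised to SD 15.
- Restate the power for the chosen margin: 99.1% at four points or 98.2% at 3.75, at SD 15, 624 per arm and one-sided 1%. If another SD is adopted, recompute on that SD.
- Label three points as a supplementary power figure and correct it to 88.6% on the same assumptions.

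The cost is wording only, with no extra participants. The three-point power becomes slightly less favourable. If four points is kept, its SD equivalent rises above 0.25; if 3.75 is chosen, the threshold is slightly stricter.
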